# 4. PATIENT ELIGIBILITY, ENROLLMENT, RANDOMIZATION, AND WITHDRAWAL

## 4.1 Patient eligibility

Each subject should meet all of the inclusion criteria and none of the exclusion criteria for this study. Under no circumstances can there be exceptions to this rule.

**4.1.1 Inclusion criteria**

For inclusion in the study, subjects should fulfil the following criteria:

1. Volunteer to participate in the study with good compliance. Able to complete the observation and follow-up and have signed the informed consent;
2. More than 18 years old with no limit of sex;
3. Pathologically confirmed stage T_4_N_0-3_ or T_1-3_N_2-3_ NSCLC with residual tumor after first-line treatment (first-line chemotherapy, targeted therapy, immunotherapy, chemotherapy combined with immunotherapy, etc.) evaluated operable for radical resection; pathologically confirmed stage IVA NSCLC evaluated operable after first-line treatment (first-line chemotherapy, targeted therapy, immunotherapy, chemotherapy combined with immunotherapy, etc.);
4. ASA score: I-III;
5. Cardiopulmonary functions meet the requirements of radical operation for lung cancer with normal liver and kidney functions.

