## 1.2 Schema

# 2. INTRODUCTION

Lung cancer is the leading cause of cancer death worldwide^1^. An estimated 2.2 million new lung cancer cases occurred in 2020, accounting for about 11.4% of total cancer diagnoses. NSCLC is the dominant type of lung cancer^2^. Approximately 80% of patients with NSCLC present with either metastatic or locally advanced disease that is not initially amenable to resection^3^.

Treatments for locally advanced NSCLC, stage III NSCLC, is controversial. Surgical resection is primarily recommended for T1-3 diseases with single station and non-bulky N2, while other stage III NSCLC are determined initially unresectable. Previous studies have shown that conversion surgery after induction therapy could bring potential benefits for these patients^4-8^. However, it requires strict operation indications and patient screening. Furthermore, this concept of treatment still needs evidence from prospective studies to prove its safety and feasibility.

This single-arm, prospective study evaluated the safety and feasibility of conversion surgery after induction therapy for initially unresectable locally advanced and advanced NSCLC patients.

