**2.2.2 Rationale for study patient**

Patients with initially unresectable NSCLC having been evaluated as operable after receiving first-line treatment are eligible for the study.

Initially unresectable clinical stage IIIA-B NSCLC is defined as T_1-3_ with multi station or bulky N_2_ and T_3-4_ N_1-0_ with invasion. All the clinical stage IIIC and IV NSCLC are initially unresectable. The Appendix 1 displays the eighth edition of the TNM classification for lung cancer.

The first-line treatments include chemotherapy, chemotherapy plus immunotherapy, and targeted therapy.

Previous studies have shown that conversion surgery after induction therapy could bring potential benefits for these patients^4-8^. Therefore, we included these patients to receive conversion surgery in our study.

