| M0 | No distant metastasis |
| M1 | Distant metastasis present |
| M1a | Separate tumor nodule(s) in a contralateral lobe; tumor with pleural or pericardial nodule(s) or malignant pleural or pericardial effusion |
| M1b | Single extrathoracic metastasis |
| M1c | Multiple extrathoracic metastases in one or more organs |

| **T/M** | Subgroup | **N0** | **N1** | **N2** | **N3** |
| --- | --- | --- | --- | --- | --- |
| **T1** | **T1a**≤1cm | IA1 | IIB | IIIA | IIIB |
|  | 1cm<**T1b**≤2cm | IA2 | IIB | IIIA | IIIB |
|  | 2cm<**T1c**≤3cm | IA3 | IIB | IIIA | IIIB |
| **T2** | 3cm<**T2a**≤4cm | IB | IIB | IIIA | IIIB |
|  | 4cm<**T2b**≤5cm | IIA | IIB | IIIA | IIIB |
| **T3** | 5cm<**T3**≤7cm | IIB | IIIA | IIIB | IIIC |
| **T4** | 7cm<**T4** | IIIA | IIIA | IIIB | IIIC |
| **M1** | **M1a** | IVA | IVA | IVA | IVA |
|  | **M1b** | IVA | IVA | IVA | IVA |
|  | **M1c** | IVB | IVB | IVB | IVB |

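### The binding eligibility criteria do not carry over the initially unresectable requirement in the aim and in section 2.2.2, and no listed data item would let the analysis separate those patients

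*Combined protocol and SAP*

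**What the plan says.** The Introduction gives the purpose as evaluating "conversion surgery after induction therapy for initially unresectable locally advanced and advanced NSCLC patients", and section 2.2 says the same. Section 2.2.2 states who is meant: "Patients with initially unresectable NSCLC having been evaluated as operable after receiving first-line treatment are eligible for the study". It then defines the term: "Initially unresectable clinical stage IIIA-B NSCLC is defined as T_1-3_ with multi station or bulky N_2_ and T_3-4_ N_1-0_ with invasion". It adds: "All the clinical stage IIIC and IV NSCLC are initially unresectable".

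The binding list is in section 4.1. Criterion 3 of section 4.1.1 reads "Pathologically confirmed stage T_4_N_0-3_ or T_1-3_N_2-3_ NSCLC with residual tumor after first-line treatment", judged operable for radical resection, with operable stage IVA as the alternative. The synopsis repeats it. Section 4.1 sets the rule: "Each subject should meet all of the inclusion criteria and none of the exclusion criteria for this study". The only exclusion in section 4.1.2 that names a prior treatment is neoadjuvant chemoradiotherapy.

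On who is a surgical candidate from the start, the Introduction says: "Surgical resection is primarily recommended for T1-3 diseases with single station and non-bulky N2, while other stage III NSCLC are determined initially unresectable". Section 2.2 says that selected single-station, non-bulky T1-3N2 patients may have systemic therapy and then be considered for surgery, and that T3-4N0-1 patients may also be considered.

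The formal objective (synopsis and section 3.1) and the hypothesis (section 7.1) name locally advanced and advanced NSCLC without the words initially unresectable.

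**The concern.** A conclusion about conversion surgery concerns patients who could not have been resected at the outset. Criterion 3 does not ask whether that was so. A patient with single-station, non-bulky N2 who has had chemotherapy or chemo-immunotherapy and is then judged operable meets it, although the Introduction places that patient among surgical candidates. There is no control arm, so the mix of patients feeds directly into every estimate: R0, morbidity, DFS and OS.

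The mix could not be sorted out afterwards from the items listed. The CRF items in section 6.1 include clinical TNM with no time point, and nothing on initial resectability, N2 stations, N2 bulk or invasion. Baseline data under section 4.2.1 run from admission to enrollment, which is after first-line treatment. The multidisciplinary discussion in the synopsis is described only for resectability after that treatment.

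**Working it through.** **No figure to reproduce.** Section 2.2.1 says the sample size of 30 was not calculated from a hypothesis test. The check has two parts.

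**1. Stage cells.** Criterion 3 admits ten M0 combinations. Set against Appendix 1 and section 2.2.2:

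| Admitted by criterion 3 | Appendix 1 stage | Under the 2.2.2 definition |
| --- | --- | --- |
| T3N3, T4N3 | IIIC | wholly inside |
| T1N2, T2N2 | IIIA | only if multi-station or bulky |
| T3N2 | IIIB | only if multi-station or bulky |
| T4N0, T4N1 | IIIA | only with invasion |
| T1N3, T2N3, T4N2 | IIIB | not covered |

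Two cells lie wholly inside, five lie inside only under conditions that criterion 3 does not ask for, and three are not covered by the wording of 2.2.2.

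In the other direction, T3N1 with invasion and stage IVB meet 2.2.2 but not criterion 3. Section 2.2.2 also lists T3N0 with invasion under IIIA-B, while the T3 row of Appendix 1 reads "5cm<T3≤7cm | IIB | IIIA | IIIB | IIIC", so T3N0 is IIB.

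For T4N0-1 the text gives three answers. The Introduction counts it as initially unresectable, being stage III other than the N2 exception. Section 2.2 says it may be considered for surgery. Section 2.2.2 requires invasion, whereas Appendix 1 allows T4 by size above 7 cm or by a separate nodule in another ipsilateral lobe.

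**2. Possible effect on R0.** From the plan: n = 30 (section 7.2) and a hypothesis of R0 above 90% (section 7.1). Since 27/30 is exactly 90%, exceeding it needs at least 28/30 = 93.3% (exact 95% CI 77.9% to 99.2%). All rates and shares below are assumptions.

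With no initially resectable patients and true R0 of 85%:

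P(X ≥ 28) = 435 × 0.85^28 × 0.15^2 + 30 × 0.85^29 × 0.15 + 0.85^30 = 0.1034 + 0.0404 + 0.0076 = 0.151.

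With k initially resectable patients at 95%, the count is the sum of Binomial(k, 0.95) and Binomial(30 − k, 0.85):

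- k = 9: expected R0 = (21 × 0.85 + 9 × 0.95)/30 = 88.0%; P(X ≥ 28) = 28.2%.
- k = 15: expected R0 = (15 × 0.85 + 15 × 0.95)/30 = 90.0%; P(X ≥ 28) = 40.8%.

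P(X ≥ 28) over a range of true R0 in initially unresectable patients, with the resectable rate held at 95%:

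| True R0, unresectable | 0 of 30 resectable | 9 of 30 | 15 of 30 |
| --- | --- | --- | --- |
| 75% | 1.1% | 5.3% | 14.1% |
| 80% | 4.4% | 13.0% | 25.0% |
| 85% | 15.1% | 28.2% | 40.8% |
| 90% | 41.1% | 52.4% | 60.7% |

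**Morbidity (primary endpoint).** If the assumed rates are 40% in unresectable and 20% in resectable patients, 9 of 30 resectable gives (21 × 0.40 + 9 × 0.20)/30 = 34%, and 15 of 30 gives (15 × 0.40 + 15 × 0.20)/30 = 30%. If both rates are 30%, there is no shift.

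**The case against.** The protocol is not silent. Section 2.2.2 states that initially unresectable patients are the ones eligible. A reader might infer from the no-exceptions rule that the team must enroll everyone who meets criterion 3. The rule does not say that. It bars patients who fail a criterion, and 2.2.2 can narrow intake without breaching it. This stands: the fault is a rationale that was not carried into the criteria, and the documents do not show that surgical candidates will be enrolled.

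A reader might also infer that every mismatch lets in easier cases. That does not follow. T3N0-1 is not admitted as M0 disease, so it cannot raise R0. T1-2N3 and T4N2 are unresectable on the wording of the Introduction and section 2.2; their absence from 2.2.2 is a gap in the definition. Whether T4N0-1 without invasion is resectable at the outset is unresolved in the text.

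The effect on results can likewise be overstated. The documents give no R0 or morbidity by initial resectability. Every patient must be judged operable for radical resection, which could narrow any difference. With assumed rates of 85% and 95%, expected R0 reaches 90% only when half the patients are initially resectable: (0.90 − 0.85)/(0.95 − 0.85) = 50%. R0 is a secondary endpoint, the 90% figure has no test or decision rule attached, and the study is declared exploratory. These points limit the severity. They do not remove the conflict over single-station, non-bulky N2, or the lack of any listed item to identify those patients.

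**Conclusion.** The concern holds as a conflict between the stated aim and the binding criteria. Criterion 3 does not require initial unresectability. The clearest consequence is that single-station, non-bulky T1-3N2 is admissible. The target population is itself stated inconsistently: the Introduction, section 2.2 and section 2.2.2 disagree on T4N0-1, 2.2.2 has gaps against Appendix 1, and the formal objective omits initial unresectability.

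A favorable shift in R0 is plausible, and one in morbidity is less certain. Neither can be sized from the documents. The rise from 15.1% to 28.2% or 40.8% rests wholly on assumed R0 of 85% and 95% and on assumed shares of 9 or 15 in 30. It shows only that, at this sample size, a few patients can decide on which side of 90% the observed rate falls. It does not support saying that R0, morbidity, DFS or OS will be biased. This should be fixed, because a conclusion about conversion cannot otherwise be tied to the patients it names.

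**What to change.** First reconcile the synopsis, the Introduction, sections 2.2, 2.2.2, 3.1 and 4.1.1, and Appendix 1 into one definition of the target population. Which patients count as initially unresectable is for the investigators; this review does not choose. The order matters: writing the present 2.2.2 wording into criterion 3 would drop T1-2N3 and T4N2.

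Then:

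- Refer to the reconciled definition in criterion 3, and state whether its TNM is the stage before first-line treatment.
- Add to the eligibility CRF, from existing records: pre-treatment clinical TNM, N2 station count, N2 bulk, invasion, and the reason for initial unresectability.
- Keep the section 7.5 analysis of all eligible enrolled patients. Beside it, report R0 and morbidity with exact 95% CIs for those who meet the reconciled definition, and base any conclusion about conversion of initially unresectable disease on that group.

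The cost is an amendment to the wording, a few CRF fields, and a somewhat smaller and less precise group for that conclusion. The sample size of 30 need not change.

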**4.1.2 Exclusion criteria**

Patients should not enter the study if any of the following preoperative exclusion criteria are fulfilled:

1. Serious heart, lung, liver and kidney dysfunction and unable to tolerate the operation;
2. Neurologic, mental illness or mental disorder which is hard to control, poor compliance, unable to cooperate or describe the treatment response;
3. Unable to receive radical resection;
4. Need of palliative or emergency operation due to lung abscess or hemoptysis;
5. Having received neoadjuvant chemoradiotherapy.

## 4.2 Patient enrollment

**4.2.1 Patient selection**

Clinical examination data of patients conducted from hospital admission to enrollment into this study (time period is usually 1 week) will be considered baseline data, and must include:

1. Systemic status: height, weight, comorbidities;
2. Peripheral venous blood: white blood cell count (WBC), hemoglobin (Hb), platelet count (PLT), lymphocyte count (LYM);
3. Blood biochemistry: albumin, prealbumin, total bilirubin, AST, ALT, creatinine, fasting glucose, CRP;
4. Serum tumor markers: CEA, CA19-9, CA72-4, NSE;
5. Contrast-enhanced chest computed tomography (CT) (slice thickness of 2.5 mm or less; in case of allergy to the contrast agent, non-contrast CT is allowed);
6. Chest X-ray (AP and lateral views): cardiopulmonary conditions;
7. Resting 12-lead ECG;
8. Respiratory function tests: FEV1, FVC, FEV1/FVC, MVV.

For patients with other comorbidities (e.g., diabetes, coronary heart disease, hypertension), corresponding examinations will be performed to exclude surgical contraindications.

For solid pulmonary nodules on normal chest CT, an FDG PET/CT scan is warranted to screen out aggressive, advanced-stage tumors. If PET/CT scan is positive in the mediastinum, lymph node status needs pathologic confirmation. Methods for pathologic confirmation of lymph node status include mediastinoscopy and endobronchial ultrasonography (EBUS).

After the above-mentioned preoperative examination, a surgery team led by [name] will discuss the possibility of surgery and how it will be done.

**4.2.2 Informed consent**

Patients will be approached for possible recruitment following clinical evaluation, provided they fulfil the patient eligibility criteria (see section 4.1). Patients who fail to meet the patient eligibility criteria should not, under any circumstances, be enrolled in this study. There can be no exceptions to this rule. Patients will be provided with verbal and written details. A verbal explanation of the trial along with the ICF will be provided by a medically qualified member of the surgery team for the patient to consider (Appendix 3). The rationale, design and personal implications of the trial will be provided and explained by the study member.

Following information provision, patients should be given the opportunity to discuss the trial with their family and healthcare professionals before they are asked whether they are willing to take part in the trial. Patients will be given as much time as possible to consider their participation in the trial. The right of the patient to refuse consent without giving reasons will be respected.

Assenting patients will then be formally assessed for eligibility and invited to provide informed written consent for their participation in the study. ICF may only be obtained by the principal investigator or another clinically qualified member of the trial team who has received GCP training and is approved by the principal investigator to take informed consent as documented in the trial log.

The patient consent form with all original signatures must be retained in the trial log. A copy of the signed ICF should be given to the patient, and a record of the consent process, detailing the date of consent and witnesses, should also be kept in the patient’s notes (this may include a copy of the ICF as per local practice).

Patients will remain free to withdraw from the trial at any time by revoking consent without giving reasons and without prejudicing any further treatment.

## 4.3 Withdrawal of study

At any time, patients are free to withdraw from the study without prejudice to further treatment. For patient who withdraws between inclusion and surgery, the patient will be excluded from the study and no further data of the patients will be recorded. For patients withdrawing after surgery, perioperative outcomes will still be recorded. They will be asked if they are willing to continue with survival follow-up (which can be conducted by telephone). If the patients wish to withdraw from the study entirely, including further follow-up, this should be clearly documented in the patient notes.

# 5. TREATMENT METHODS

## 5.1 Preoperative investigation and preparation

Preoperative investigation and preparation will be accorded with the routine clinical work in the department of thoracic surgery, Ruijin Hospital affiliated Shanghai Jiao Tong University School of Medicine (see section 4.2.1).

## 5.2 Surgery

All surgeries will be performed under general anesthesia with double-lumen endotracheal intubation. The specifics of each operation will be at the discretion of the operating surgeon (e.g., port placement, lymph node dissection), as will the decision to convert to an open operation. There are, however, basic standard of surgical procedures, which are described in the following sections.

**5.2.1 Robot-assisted thoracic surgery (RATS)**

RATS is performed using a da Vinci S/Si surgical robot (Intuitive Surgical, Inc, Santa Clara, CA). Five ports are placed in the following positions: a 12-mm camera port is placed in the eighth ICS at the mid-axillary line; three 8-mm working ports are placed separately in the fifth ICS at the anterior axillary line (#1 arm), the eighth ICS at the posterior axillary line (#2 arm), and the eighth ICS at 2 cm lateral to the spine (#3 arm). Finally, the auxiliary port is placed in the eighth ICS between the camera port and the anterior port.

**5.2.2 Video-assisted thoracic surgery (****VATS)**

VATS is performed through a 4-cm incision, which is placed in the fifth ICS at the anterior axillary line and covered with a protective sleeve. Uniportal VATS is preferred over multiportal VATS. When necessary, an additional auxiliary port will be placed in the sixth or eighth ICS at the mid-axillary line. All surgical instruments are inserted through the incision without spreading the ribs.

**5.2.3 Thoracotomy**

Thoracotomy is performed through muscle sparing (MS) incision, which is placed in the fifth ICS at the anterior axillary line.

**5.2.4 Regulations on conversion to** **thoracotomy**

When intra-thoracic hemorrhage, organ damage and other serious/life-threatening complications which are difficult to control occur during the procedure of RATS and VATS, it is necessary to actively convert to thoracotomy. The surgeon in charge can decide to convert to thoracotomy for other technical or equipment reasons. The reasons for all cases of conversion to thoracotomy must be clearly recorded in the case report forms (CRFs). The incision length for the conversion to thoracotomy is not regulated in this study.

**5.2.5 Lymph node dissection**

Appropriate N1 and N2 lymph node stations should be dissected for each patient. Mediastinal nodal staging must be accomplished by dissection of a minimum of three N2 stations for all patients.

## 5.3 Postoperative management

Enhanced recovery after surgery (ERAS) is routinely implemented, including smoking cessation, breathing training, analgesia, early postoperative activities, early postoperative extubation, etc.

**5.3.1 Preventive use of analgesics**

Patient-controlled analgesia and oral nonsteroidal anti-inflammatory drugs are given routinely for postoperative analgesia. Intravenous nonsteroidal anti-inflammatory drugs, meperidine, and tramadol are used as extra-analgetic according to specific patient conditions.

**5.3.2 Preventive use of antibiotics**

Postoperative prophylactic intravenous antibiotics is routinely used, which are the second generation cephalosporins. For patients who are allergic to cephalosporins, clindamycin will be used instead. The preventive use of antibiotics usually lasts for 24 hours, and hardly exceeds 48 hours. The specific use of antibiotics will be based on doctor’s experience and routine practices.

**5.3.3 Fluid replacement**

Postoperative fluid infusion (including glucose, insulin, electrolytes, vitamins, etc.) will be performed based on doctor’s experience and routine clinical practices, and is not specified in this study. After oral feeding, it is allowable to stop or gradually reduce fluid infusion/nutritional support.

**5.3.****4 Discharge**

The nursing and rehabilitation therapists ensure that patients are mobilized on the day of surgery or as soon as possible. With the help of the rehabilitation therapists, the patients are encouraged to do the chest expansion exercises, segmental breathing, and respiratory muscle training. In the absence of postoperative complications, abnormality on postoperative chest X-rays and fever, the patient can be discharged, which should be recorded in the CRFs. On discharge, patients are asked to contact the thoracic ward if concerns arise.

## 5.4 Postoperative adjuvant therapy

The principle of adjuvant therapy is in accordance with the national comprehensive cancer network guideline for NSCLC^11^. Postoperative adjuvant therapy is recommended for patients with high-risk pathological stage IB, and pathological stage IIA or later stages. High-risk factors may include poorly differentiated tumors (including lung neuroendocrine tumors [excluding well-differentiated neuroendocrine tumors]), vascular invasion, visceral pleural involvement. These factors independently may not be an indication and may be considered when determining treatment with adjuvant chemotherapy. For patients who have indications for adjuvant therapy, adjuvant therapy is recommended but not mandatory, which is at discretion of the patients. As the guideline is keeping updating, the indication and regimen of adjuvant therapy may change as well. In general, we will follow the latest guideline, although there may be some differences due to the unavailability of certain drugs.

# 6. ASSESSMENT AND DATA COLLECTION

## 6.1 Preoperative assessments and data collection

Preoperative investigation and preparation will be accorded with the routine clinical work in the department of thoracic surgery, Ruijin Hospital affiliated Shanghai Jiao Tong University School of Medicine (see section 4.2.1).

Data collected on the randomization, eligibility and preoperative CRFs will include:

1. Personal details and demographics including height, weight, and gender;
2. Preoperative investigations performed;
3. Clinical TNM staging (the eighth edition of the TNM classification for lung cancer^12^, Appendix 1);
4. Confirmation of eligibility;
5. Confirmation of written informed consent;
6. Date of randomization;
7. Known concomitant diseases and co-morbidities;
8. Smoking status (smoking index (number of cigarettes smoked per day multiplied by years of tobacco use) is used to evaluate the smoking status of the patient).

